### Aim 1 (b)

For Aim 1 (b), we aim to devise a method to efficiently and automatically choose operators and periods for temporally aggregating clinical attributes. Our design paper [24] outlines our method for automating the process of temporally aggregating clinical attributes. We will flesh out our method’s technical details. Our automation method needs disease-specific knowledge on aggregation operators and periods compiled by clinicians and stored in Auto-ML. Various medical datasets use differing schemas, medical coding systems, and medical terminologies, forming a hurdle in applying precompiled knowledge. To tackle this, the automated temporal aggregation function of Auto-ML demands that the dataset, except for the dependent variable, complies with the Observational Medical Outcomes Partnership (OMOP) common data model [88] and its linked standardized terminologies [89]. Since OMOP standardizes administrative and clinical attributes from 10 or more large US health care systems [90,91], Auto-ML can be adopted for datasets from those systems. We intend to include support for the National Patient-Centered Clinical Research Network (PCORnet) [92] and Informatics for Integrating Biology and the Bedside (i2b2) common data models [93] in the future.

### Aim 1 (c)

For Aim 1 (c), we aim to continuously show, as a function of time given for model selection, forecasted model accuracy and projected patient outcomes of model use. During automatic selection, to be more useful and user friendly, Auto-ML will show projected patient outcomes of model use and forecasted model accuracy as a function of time given for model selection (see Figure 3). Our design paper [24] outlines our method for doing this. We will flesh out our method’s technical details and write a user manual for Auto-ML.

**Figure 3 figure3:**
[figure not shown]
The highest model accuracy gained by Auto-ML over time.

### Aim 1 (d)

#### Overview

For Aim 1 (d), we aim to validate Auto-ML on seven benchmark modeling problems. We will perform tests with health care researchers using seven modeling problems and datasets that we worked on before. Each problem uses a different dataset from a distinct health care system. We chose these problems because they are related to common diseases, are clinically important, and have readily accessible datasets. Auto-ML can be used for other clinical activities.

#### Subject Recruitment

Via announcements in our institution’s email lists and personal contact, we will recruit 25 health care researchers from UWM, which houses approximately 2500 faculty members, most doing health care research. These health care researchers would regard their familiarity with medical data at the MD level, but would regard their machine learning knowledge as below the level taught in a typical machine learning course for computer science undergraduates. We will conduct purposeful sampling to ensure enough variability [94]. All test participants will have fulfilled UWM’s required training for information security and privacy policy. Participants will receive pseudonyms linking their responses to questions for privacy protection. After giving consent, each will get a copy of the task description, Auto-ML’s user manual, and the metadata document detailing the attributes in the dataset. Upon task completion, each will receive US $200 as compensation for participation.

#### Computing Environment

We will perform all of our experiments on a Health Insurance Portability and Accountability Act (HIPAA)-compliant computer cluster at the University of Washington. After obtaining proper authorization, all test participants and research team members at the University of Washington will be able to access the cluster using their university computers.

#### Modeling Problem 1

Modeling Problem 1 will consist of predicting the diagnosis of type 2 diabetes in adult patients in the next year.

##### Dataset and Patient Population

The clinical and administrative dataset is deidentified and publicly available from the Practice Fusion Diabetes Classification Challenge [15,34], containing 3-year (2009-2012) records as well as the labels of 9948 adult patients from all US states in the following year. A total of 1904 of these patients had a diagnosis of type 2 diabetes in the following year. The dataset comes from an electronic medical record vendor’s EDW; includes repeatedly recorded attributes; and covers patient demographics, allergies, diagnoses, immunizations, medications, smoking status, lab results, and vital signs. We will put this dataset in the OMOP common data model form with its linked standardized terminologies.

##### Model Information

The dependent variable is whether a patient had a diagnosis of type 2 diabetes in the following year. Two-thirds of patients will be randomly selected and put into the training set to construct models. The remaining one-third of patients will form the test set for assessing model performance. We will use the area under the receiver operating characteristic curve (AUC) [19] performance metric.

#### Modeling Problems 2-7

Each of the six problems from Modeling Problems 2-7 uses a distinct, deidentified, and publicly available dataset from the University of California, Irvine machine learning repository [95] to perform a task: (1) Arcene: classify mass spectrometric data into cancer versus normal patterns; (2) Arrhythmia: classify 12-lead electrocardiogram recordings into one of 16 groups about cardiac arrhythmia; (3) Cardiotocography: classify fetal cardiotocograms into one of three fetal states; (4) Diabetic Retinopathy Debrecen: use features obtained from the Messidor image set to detect whether an image includes signs of diabetic retinopathy; (5) Mammographic Mass: use Breast Imaging Reporting and Data System attributes and patient age to separate benign from malignant mammographic masses; (6) Parkinson Speech: use sound recordings to identify Parkinson’s disease patients.

No dataset has repeatedly recorded attributes needing temporal aggregation. The repository [95] includes a detailed description of the problems and datasets. For each dataset, two-thirds of it will be randomly selected and put into the training set to construct models. The remaining one-third will form the test set for assessing model performance. We will use the accuracy metric suitable for multi-class classification.

#### Performance Evaluation and Sample Size Justification

We will test the hypothesis that at least 60% of health care researchers can use Auto-ML to achieve model accuracy of at least 95% of the gold standard. When 60% of health care researchers can actually achieve model accuracy of at least 95% of the gold standard, a sample size of 25 health care researchers produces a one-sided 95% lower confidence limit of 42%.

#### User Feedback

When model construction is finished, we will use both open-ended and semistructured questions to survey the 25 health care researchers. As detailed in our design paper [83], we will obtain quantitative outcome measures covering model accuracy, time on task, self-efficacy for constructing machine learning models with clinical big data, satisfaction, trustworthiness, adequacy, and quality of documentation. The questionnaire will contain a text field for gathering comments on Auto-ML. We will refine and finalize Auto-ML by considering suggestions from those comments. We will perform a user satisfaction survey using the System Usability Scale (SUS), a widely used industry standard [96,97] on overall satisfaction ratings for products.

#### Analysis

We will use the accepted inductive approach endorsed by Patton et al [94,98] to do qualitative analysis. We will put the 25 health care researchers’ textual comments into ATLAS.ti Version 8 (ATLAS.ti Scientific Software Development GmbH), a qualitative analysis software tool [99]. The research team will independently highlight quotations related to the issue of using Auto-ML. We will examine quotations, categorize them into precodes, and merge them into categories in multiple iterations. We will synthesize categories to find general themes. Quantitative analyses will include adding the scores in the SUS and presenting every quantitative outcome measure’s descriptive statistics.

### Aim 2

**Overview** Aim 2 involves applying Auto-ML and novel methodology to two new modeling problems crucial for care management allocation, to which our institutions are seeking solutions, and pilot one model with care managers. Both modeling problems use datasets that have repeatedly recorded attributes. We will put the datasets in the OMOP common data model form with its linked standardized terminologies. We will use the same computing environment and recruiting method mentioned in Aim 1 (d). We will recruit two health care researchers not engaged in Aim 1 (d). Each will be randomly given a problem and use Auto-ML to build models for it. Upon task completion, each will receive US $200 as compensation for participation.

#### Modeling Problem 8

Modeling Problem 8 involves the use of vast attributes in modern IH electronic medical records to predict hospital use in asthmatic children in the next year.

##### Patient Population

The patient population consists of IH pediatric patients (0-17 years of age) with asthma in 2005-2016, identified by Schatz et al’s method [63,100,101] as having the following: (1) at least one diagnosis code of asthma according to the International Classification of Diseases, Ninth Revision (ICD-9) (ie, 493.xx), or the International Classification of Diseases, Tenth Revision (ICD-10) (ie, J45/J46.*); or (2) two or more “asthma-related medication dispensings (excluding oral steroids) in a one-year period, including β-agonists (excluding oral terbutaline), inhaled steroids, other inhaled anti-inflammatory drugs, and oral leukotriene modifiers.”

##### Dataset

By running Oracle database Structured Query Language (SQL) queries, our contracted IH data analyst will extract from the IH EDW a deidentified, clinical and administrative dataset, encrypt it, and securely transfer it to a HIPAA-compliant computer cluster for secondary analysis. For each of the last 5 years, the data cover approximately 27,000 asthmatic children. The dataset is the electronic documentation of approximately 95% of pediatric care in Utah [102,103] and includes around 400 attributes partially listed in our paper [14]. These attributes cover many known risk factors for hospital use in asthma and can be used to find new predictive factors.

##### Model Information

The dependent variable is whether an asthmatic patient incurred hospital use—inpatient stay or ED visit—with a primary diagnosis of asthma (ie, ICD-9 493.xx or ICD-10 J45/J46.*) in the following year [14,63,64]. As outcomes need to be computed for the following year, we effectively have 11 years of IH data. We will construct models using the data in the first 10 years and acquire a model’s accuracy estimate via testing on the data in the 11th year. This mirrors future use of the model in practice. We will use the AUC [19] performance metric.

#### Modeling Problem 9

Modeling Problem 9 involves using UWM’s incomplete data to predict individual diabetic adults’ costs in the next year.

##### Patient Population

The patient population includes UWM adult patients (18 years of age or older) with diabetes in 2012-2016, identified by the method in Neuvirth et al [104] as having one or more hemoglobin A1c test results of 6.5% or higher.

##### Dataset

A UWM data analyst will run SQL Server database SQL queries to extract from the UWM EDW a deidentified, clinical and administrative dataset, encrypt it, and securely transfer it to a HIPAA-compliant computer cluster for secondary analysis. The data cover approximately 28,000 diabetic adults per year. Other details of the dataset are similar to those in Modeling Problem 8.

##### Model Information

The dependent variable is a diabetic patient’s total allowed cost to UWM in the following year [60,61]. Allowed costs are less inflated than billed costs and less subject to variation due to member cost sharing than net incurred claims [60]. We will adopt the medical consumer price index [105] to convert all costs to 2016 US dollars to handle inflation. As outcomes need to be computed for the following year, we effectively have 4 years of UWM data. We will construct models using the data in the first 3 years, and acquire a model’s accuracy estimate via testing on the data in the 4th year. This mirrors future use of the model in practice. We will use the *R*^2^ performance metric [61].

To fill the scope gap mentioned in the introduction, we will use a constraint to find patients who tend to get most of their care at UWM. Intuitively, it is easier to identify future high-cost patients among them than among others. We will use UWM’s incomplete data to build a cost prediction model and apply it to them. Regardless of his/her total future cost at non-UWM facilities, a patient who will incur high cost at UWM can be a candidate for care management. By care managing future high-cost patients identified by the model, we will expand the scope of using care management to improve outcomes. The principle of our approach to using incomplete data generalizes to many other clinical applications.

Several candidate constraints exist: (1) the patient had two or more visits to UWM in the past year, (2) the patient has a UWM primary care physician and lives within 5 miles of a UWM hospital, and (3) the patient saw a primary care physician or endocrinologist at UWM in the past year and lives within 60 miles (ie, around 1 hour of driving distance) of a UWM hospital. UWM primary care physicians tend to make referrals within UWM. Endocrinologists often serve some of the same roles as primary care physicians. Usually, a patient incurs high cost because of hospital use. As patients living far away from UWM hospitals are less likely to use them, UWM tends to have less of these patients’ medical data. We will refine the three candidate constraints and investigate others. To select the constraint to be used, we will use PreManage data that UWM has on all of its patients. PreManage is Collective Medical Technologies Inc’s commercial product providing encounter and diagnosis data on inpatient stays and ED visits at many US hospitals [106]. PreManage data cover 105 (approximately 94%) hospitals in Washington, including the four hospitals of UWM. Using UWM data and grouper models like the Clinical Classifications Software system to group diagnosis codes and reduce features [60], we will build two models: one for estimating an inpatient stay’s allowed cost and another for estimating an ED visit’s allowed cost based on patient demographics and diagnosis data. We will use UWM patient demographics data, PreManage diagnosis data, and the two models to estimate the allowed cost of each of a UWM patient’s non-UWM inpatient stays and ED visits reflected by PreManage encounter data. By aggregating the estimated costs of individual non-UWM inpatient stays and ED visits, we will assess each UWM patient’s portion of cost spent at non-UWM hospitals and use the portions to evaluate every candidate constraint. If a health care system does not have enough data to make the two models reasonably accurate, it can use the average costs of an inpatient stay and ED visit to assess each patient’s portion of cost spent at external hospitals. If a system has an insurance plan’s complete claim data on some of its patients, it can use the data similarly.

#### Performance Evaluation and Sample Size Justification

For each of the two new modeling problems, we will test the hypothesis that health care researchers are able to use Auto-ML to achieve higher model accuracy than existing approaches. We will regard Aim 2 as partly successful if we accept the hypothesis in only one problem, and completely successful if we accept the hypothesis in both problems.

For Modeling Problem 8, we will compare the accuracies reached by the model built by the health care researcher and the model in Schatz et al [65]. The first model is built using Auto-ML and vast attributes in modern IH electronic medical records. The second model depicting the existing approach was built using a few known risk factors for hospital use in asthma. Using vast attributes can increase prediction accuracy [107]. We will accept the hypothesis when the first model reaches a higher AUC than the second one by at least .05. Existing predictive models for hospital use in asthma usually achieve an AUC far below .8 [63-68]. Assuming these two models’ prediction results have a correlation coefficient of .6 for both classes and performing a two-sided *Z* test at a significance level of .05, a sample size of 561 data instances per class provides 90% power to find a discrepancy of .05 between the two models’ AUCs. The IH data in the 11th year include about 27,000 asthmatic children, offering enough power to test our hypothesis. Using many patients is essential for improving prediction accuracy, although only a small sample size is needed to show statistical significance.

For Modeling Problem 9, we will compare the accuracies gained by two models. The patient cohort includes those satisfying the chosen constraint. The first model is built by the health care researcher using Auto-ML and clinical and administrative data. The second model depicting the existing approach is a commercial claims-based one available at UWM achieving an *R*^2^ less than 20%. Although the second model was not designed for such use, we will apply it to the patient cohort on whom UWM possibly has incomplete data, which is better than the normal practice of making no predictions. Adding clinical data can increase prediction accuracy [108]. We will accept the hypothesis when the first model reaches a higher *R*^2^ than the second one by at least 5%. Using an *F* test at a significance level of .05 and under the assumption of the existence of 20 features from clinical data in addition to 300 or fewer features used in the second model, a sample size of 443 patients provides 90% power to identify an increase of 5% in *R*^2^ from 20%. Using the second candidate constraint, we estimate that the patient cohort will cover approximately 22% of diabetic adult patients at UWM. The 4th year’s UWM data include approximately 28,000 diabetic adults, offering enough power to test our hypothesis.

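### Aim 2's 90% power is for tests of zero difference; under the stated acceptance rule, the chance of acceptance at the same true gains is about 50%

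*Protocol article*

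**What the plan says.** All of this stands in the protocol article, Methods, Aim 2, Performance Evaluation and Sample Size Justification.

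- **Hypothesis, for each problem:** "we will test the hypothesis that health care researchers are able to use Auto-ML to achieve higher model accuracy than existing approaches".
- **Rule, Modeling Problem 8:** "We will accept the hypothesis when the first model reaches a higher AUC than the second one by at least .05".
- **Power, Modeling Problem 8:** "a sample size of 561 data instances per class provides 90% power to find a discrepancy of .05" between the AUCs, assuming that the models' "prediction results have a correlation coefficient of .6 for both classes" and "performing a two-sided *Z* test at a significance level of .05". About 27,000 children are available in the test year, and the article concludes that this is adequate for the hypothesis.
- **Rule, Modeling Problem 9:** accept when the new model's R-squared is higher "than the second one by at least 5" per cent.
- **Power, Modeling Problem 9:** an F test at .05 with 443 patients has 90% power for a 5-point increase from 20%, with 20 added features on top of up to 300. The cohort is put at about 22% of roughly 28,000 adults, and the same conclusion on power is drawn.

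Aim 2 counts as fully or partly successful according to whether both hypotheses or only one are accepted. The Model Information sections fix that accuracy is measured on a held-out final year.

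**The concern.** In both problems the number used as the acceptance bar is also the true gain at which power was computed. A test of zero difference with 90% power rejects at observed gains well below the gain it was powered for. The acceptance rule does not: it demands that the observed gain itself reach that value. The 90% therefore describes one procedure while Aim 2 is decided by another.

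At stake is how a negative result is read. The hypothesis is that accuracy is higher. Under the rule, a real gain at or somewhat below the bar is often or usually not accepted, although the test that was powered would detect it. A reader relying on the article's power statement would take such a failure as stronger evidence against the method than it is.

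**Working it through.** **Inputs from the article.** Two-sided alpha .05; power 90%; true AUC gain .05; correlation .6; 561 per class; R-squared 20% to 25%; 20 tested and 300 other features; 443 patients; about 27,000 children; a cohort of .22 × 28,000 = 6,160 adults.

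**Not given, so assumed.** The baseline AUC (the article says only "Existing predictive models for hospital use in asthma usually achieve an AUC far below .8") and the event rate in the asthma test year.

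**1. Reproduce the plan's figures.**

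- *F test:* f² = .05/(1 − .25) = .0667. Noncentrality = 443 × .0667 = 29.5. Degrees of freedom are 20 and 443 − 300 − 20 − 1 = 122. Power = .9001, and 443 is the smallest n reaching 90%. The figure reproduces exactly, which shows that the null is zero gain.
- *Z test:* the required n depends on the unstated baseline. For baselines from .55 to .80, with several variance formulas, n runs from about 275 to 590. A baseline of .60 against .65 gives 559 or 560, close to 561.

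**2. What the powered Z test requires.** At 90% power, SE = .05/(1.960 + 1.282) = .0154. The test rejects at an observed gain of 1.960 × .0154 = .030. The rule asks for .05, so the rule is what binds. Requiring significance as well would change nothing, because an observed .05 is already significant.

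**3. Acceptance when the true gain equals the bar.** P(observed ≥ .05 | true .05) = 1 − Φ((.05 − .05)/SE) = 1 − Φ(0) = .50, whatever the SE.

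Simulation check for AUC (paired binormal scores, correlation .6, DeLong variance):

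| Events / non-events | AUCs | Accepted under rule | Z test significant |
|---|---|---|---|
| 561 / 561 | .75 vs .80 | .499 | .98 |
| 561 / 561 | .70 vs .75 | .498 | .95 |
| 561 / 26,439 | .75 vs .80 | .52 | 1.00 |
| 1,350 / 25,650 | .75 vs .80 | .48 | 1.00 |

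Simulation check for held-out R-squared, 20% vs 25%: acceptance .50 (n = 443) and .51 (n = 6,160) with normal errors; .56 and .54 with skewed errors.

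**4. True AUC gain needed for 90% acceptance: .05 + 1.282 × SE.**

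- 561 per class: .05 + 1.282 × .0154 = .070.
- 27,000 children, with SEs from a binormal simulation at AUC .75 vs .70 and correlation .6:
  - assumed rate 2.1% (567 events), SE .0095: .062
  - assumed rate 5.0% (1,350 events), SE .0064: .058
  - assumed rate 8.7% (2,349 events), SE .0050: .056

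**5. Either side of the bar, with the same three SEs (.0095, .0064, .0050).**

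- True gain .06: Φ(.01/SE) = about 85%, 94%, 98%. At 561 per class (SE .0154) it is about 74%.
- True gain .04: 1 − Φ(.01/SE) = about 15%, 6%, 2%. The Z test of zero difference would have about 99% power or more there.

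**The case against.** The best reply is that the article makes no arithmetical error. It ties the 90% to a named Z test and a named F test, and both figures hold for those tests. It never states a 90% chance of meeting the acceptance rule. The bar may be a deliberate minimum-performance requirement, and any threshold on a point estimate is passed about half the time when the truth sits exactly on it. Nothing says that the expected gain is exactly .05 or 5 points. The rule is also stricter than the test, so it does not make false acceptance of zero gain more likely. All of this stands. It does not make the 90% apply to the rule, and the article goes on to claim adequate power for hypotheses that the rule decides.

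Some stronger readings are tempting, and the documents do not support them:

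- *That more test data cannot help.* This is true only at the bar; below it, more data lowers acceptance. Above it, more data helps: at a true AUC gain of .06, acceptance rises from about 74% at 561 per class to about 85% to 98% under the assumed event rates.
- *That full success in both problems has a 25% chance instead of 81%.* The article states no joint power. Both figures need independence, and the 25% also needs both true gains to sit exactly at the bar.
- *That 50% is the plan's overall chance of success.* The text closing Aim 2 allows a revised dependent variable for Modeling Problem 9, and another researcher if the first does not build a reasonably accurate model. These fallbacks change the overall probability, but do not restore the 90%.

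**Conclusion.** The point holds as a mismatch between the powered tests and the decision rule. The 90% figures are right for detecting a non-zero difference. Under the stated rule, acceptance at the same true gains is about 50%: simulated 48% to 52% for AUC, and 50% to 56% for held-out R-squared, the upper end with skewed errors. This does not depend on test-set size, and for AUC it does not depend on the baseline or the event rate. The claim of adequate power for the hypotheses therefore does not follow from the figures given.

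The .056 to .062 range is softer. It rests on assumed event rates of 8.7% to 2.1% and an assumed AUC pair of .75 vs .70. The .070 figure needs only the SE implied by the article's own 90% at 561 per class.

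**What to change.** Choose one of two repairs before test-year results are seen, since choosing afterwards would be data-driven.

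1. **Keep the bar.** State that the 90% refers only to detecting a non-zero difference. State that acceptance is about 50% when the true gain equals the bar. Give the true gain needed for 90% acceptance: about .070 AUC at 561 per class, and about .056 to .062 with 27,000 children, with the assumed event rates shown. Compute the R-squared counterpart for the held-out cohort of roughly 6,160 patients.
2. **Match the rule to the stated hypothesis of higher accuracy.** Accept when the paired 95% confidence interval for the test-year gain lies above 0, and report separately whether .05 or 5 points was reached. The downside is a lower success bar: with SEs of .0050 to .0095, observed AUC gains of about .010 to .019 (1.96 × SE) would suffice. Whether that is acceptable is for the sponsor to decide.

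Either repair costs a few sentences and one short calculation. No further data are needed and no sample size changes, because the available records fix the test-set size. Under the first repair, the stated power becomes less favourable.

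### Modeling Problem 9 is sized with a nested F test that does not match the planned held-out comparison, so 90% power at 443 patients is not established, and the 5-point acceptance rule is met only about half the time at the assumed effect

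*Protocol article*

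**What the plan says.** All of this is in the Protocol article, Methods, Aim 2.

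- **Sizing** (Performance Evaluation and Sample Size Justification). The calculation is an F test at the 5% level. Its model terms are fixed "under the assumption of the existence of 20 features from clinical data in addition to 300 or fewer features used in the second model". The resulting claim reads: "a sample size of 443 patients provides 90% power to identify an increase of 5% in *R*^2^ from 20" percent.
- **Comparator** (same section). The second model is "a commercial claims-based one available at UWM achieving an *R*^2^ less than 20" percent. On its use: "Although the second model was not designed for such use, we will apply it to the patient cohort". Refitting is not mentioned.
- **New model** (same section). A health care researcher builds it with Auto-ML from clinical and administrative data. Under Aim 1, Auto-ML's Machine Learning Functions, the software is to offer every Weka algorithm, so the model need not be a linear regression.
- **Evaluation** (Modeling Problem 9, Model Information). Models are built on the first 3 years, with the "accuracy estimate via testing on the data in the 4th year".
- **Decision rule** (Performance Evaluation and Sample Size Justification). "We will accept the hypothesis when the first model reaches a higher *R*^2^ than the second one by at least 5" percent.
- **Cohort** (same section). The second candidate constraint is expected to keep about 22% of roughly 28,000 diabetic adults in the 4th year. The article concludes that this gives enough power.

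**The concern.** The F test for an increase in R-squared compares two least-squares models fitted to the same patients, where the larger model contains every term of the smaller. Its 20 numerator degrees of freedom are the 20 added coefficients.

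The planned comparison has none of these features. The commercial model exists already and is applied to the cohort. The Auto-ML model is built separately and is not the commercial model plus 20 terms. The evaluation as described only scores predictions in year 4; it estimates no regression coefficients there. The precision of a difference in held-out R-squared depends on how closely the two sets of predictions agree and on the tail of the cost distribution. The F test calculation uses neither.

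Two things are at stake. First, the conclusion that power is sufficient rests on a calculation for a different test. Second, the acceptance rule demands an observed gain of at least the same 5 points that the sizing assumes as the true gain, and a power figure against zero says nothing about how often that rule is met. This hypothesis is one of the two that decide whether Aim 2 is called partly or completely successful.

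**Working it through.** **Step 1. Reproduce 443.** Inputs from the article: alpha .05, 20 added features, 300 base features, R-squared .20 to .25.

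- Effect size: f² = (.25 − .20)/(1 − .25) = .0667
- Degrees of freedom: 20 and 443 − 320 − 1 = 122
- Noncentrality: 443 × .0667 = 29.5
- Power: .9001, and 443 is the smallest N that reaches .90

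The arithmetic is correct. It implies 321 coefficients (320 features and an intercept) fitted to 443 patients.

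**Step 2. Power of the held-out comparison, normal costs.** Let y be cost scaled to variance 1, and let a and b be two fixed, calibrated predictions with R-squared .25 and .20 and correlation r. The article does not give r, so it is varied. For each patient, the difference in squared error is D = (y − b)² − (y − a)² = (a − b)(2y − a − b), with mean .05. With c = r√(.25 × .20) = .2236r:

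- Var(a − b) = .45 − 2c
- Var(2y − a − b) = 4 + .45 + 2c − 4(.45) = 2.65 + 2c
- Covariance of the two factors = .05
- SD(D) = √[(.45 − 2c)(2.65 + 2c) + .05²]
- Power, two-sided 5% test against zero = Φ(.05√N/SD − 1.96)

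Worked case, r = .894: c = .20 and SD = √(.05 × 3.05 + .0025) = .394. At N = 443 this gives Φ(2.67 − 1.96) = 76%. Simulation gives 77%.

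| r | SD(D) | Power at 443 | Power at 6,160 | N for 90% |
|---|---|---|---|---|
| .30 | .939 | 20% | 99% | 3,707 |
| .60 | .730 | 30% | >99% | 2,239 |
| .80 | .529 | 51% | >99% | 1,177 |
| .894 | .394 | 76% | >99% | about 650 |
| .93 | .327 | 90% | >99% | 450 |
| .95 | .283 | 96% | >99% | 336 |

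The value r = √(.20/.25) = .894 is the nested case, where the smaller model's prediction is a component of the larger one. Above it, the commercial prediction would carry a negative weight once the Auto-ML prediction is known, because .20 − .2236r < 0. That is possible but unusual.

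**Step 3. Skewed costs (assumption).** The article gives no cost distribution. The figures below assume lognormal costs with nested predictions at the same two R-squared values, and a simulated paired test against zero (8,000 runs at 443, 4,000 at 6,160). CV is the coefficient of variation of cost.

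| Cost CV | Power at 443 | Power at 6,160 | SD of the R-squared difference at 6,160 |
|---|---|---|---|
| 1.0 | 43% | >99% | .007 |
| 1.5 | 26% | 99% | .011 |
| 2.0 | 16% | 90% | .016 |
| 2.5 | 12% | 70% | .022 |

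The expected cohort is .22 × 28,000 = 6,160, about 14 times 443. The 22% is given for the second candidate constraint only, and the constraint is not yet chosen.

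**Step 4. The written rule.** If the true gain is .05, the observed gain is centred near .05. The probability that it reaches .05 is about 50% whatever the sample size; simulated values run from 49% to 51% at both 443 and 6,160. For roughly a 90% chance of acceptance, the true gain must be about .05 + 1.28 × SD. At 6,160 that is .05 + 1.28 × .0048 = .056 for normal costs with nested predictions, and .05 + 1.28 × .0156 = .070 for lognormal costs with CV 2.0.

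**The case against.** The strongest defence is that the defect has little practical effect. The study uses existing records, nobody is enrolled to reach 443, and the expected cohort is about 14 times larger. At 6,160 a true gain of .05 is distinguishable from zero with about 90% power or more in every scenario above except lognormal costs with CV 2.5. This stands, and it limits the severity.

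Four stronger readings are tempting, and the document does not support them.

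- *That 443 is miscalculated.* It is exact for the test named. The choice of test is what fails.
- *That 443 patients cannot give 90% power.* With normal costs and a prediction correlation of about .93 or more, they would. The document gives neither the correlation nor the cost distribution, so the supportable statement is that 90% is not established and is probably lower.
- *That the study is underpowered.* This holds at the expected cohort only under heavy assumed skew, or if the chosen constraint keeps far fewer patients. Skewed costs are plausible, since the article attributes high cost mainly to hospital use, but it reports no skewness or CV.
- *That an invalid F-test p value will decide the hypothesis.* The F test appears only in the sizing sentence. The stated decision rule is the observed 5-point gain. An F-test p value on year-4 predictions would not be valid, but the article does not clearly plan one.

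**Conclusion.** The mismatch stands and can be read directly from the text: a nested in-sample F test is used to justify a held-out comparison of two separately built models. The 90% power at 443 patients is not a property of that comparison. Across the scenarios tried, power at 443 runs from about 12% to 96%, and it reaches 90% only when the two models' predictions correlate at about .93 or more and costs are near normal. These magnitudes rest on assumed correlations, assumed cost distributions and calibrated predictions, so confidence in them is lower than in the mismatch itself.

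The acceptance probability of about 50% at a true gain of exactly 5 points depends much less on those assumptions. It follows from the rule and the effect size that the article itself states, and a larger cohort does not change it.

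This should be fixed. It concerns the justification and the decision rule; the models and the data are unaffected.

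**What to change.** 1. Delete the F test and the statement that 443 patients provide 90% power.
2. Compare the two models with a confidence interval for the difference in year-4 R-squared, from a bootstrap that resamples patients and keeps both models' predictions for each patient together.
3. State the margin that the lower limit must exceed (zero, 5 points or another value) and reconcile it with the rule of an observed gain of at least 5 points. If that rule stays, state the true gain at which it is met with acceptable probability.
4. Restate the expected precision, or the probability of acceptance, for about 6,160 patients and for the other candidate constraints. Use the cost distribution and paired squared errors from the training years, and state the assumed prediction correlation and cost distribution.

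The cost is a change of wording and a short computation, with no additional patients. The drawback is that the sample-size justification becomes less favourable than the one now printed.
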